## Methods/design

### Design

Our goal was to develop a DE-HBWC program for patients with chronic wounds, using scientific research methods. The study was a prospective study with a multi-stage mixed-methods design combining qualitative and quantitative research, following the five steps of the PEDALs model research paradigm (Figure 1). Qualitative methods included face-to-face one-on-one semi-structured interviews, literature review, and meetings with experts. The quantitative method comprised a parallel, two-armed randomized controlled trial design, with a 1:1 allocation ratio between the test and control groups for allocation concealment as well as blinding of assessors and statistical analysts.

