### Sample

The recruitment and screening of all participants were conducted on the online platform of Fujian Provincial Hospital’s WeChat official account or the hospital’s offline wound treatment clinic. This is a randomized controlled trial consisting of two branches and three evaluation stages (T0, baseline; T1, 12-week post intervention; T2, 24-week follow-up). The intervention-group participants received DE-HBWC project wound treatment at their own homes, while the control group participants received treatment at traditional hospital wound-treatment clinics. The required sample size was estimated using PASS v15.0 (NCSS, LLC, United States), based on a completely random design, to compare the mean values of two independent samples. Based on our previous wound treatment results for the healing time of chronic wounds and using two-sample T-tests assuming equal variance procedure of PASS v15.0, μ1 = 38.64, μ2 = 32.54, *σ* take 8.21, a sample size of 40 participants per group was determined to be sufficient to detect an effect with a type 1 error rate of 5 and 90% power. Assuming a drop-out rate of 20%, a total of 100 participants will be needed, with 50 participants in each group.

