### Data collection and statistical analysis

Enrolled subjects will be scheduled to complete the baseline data collection. Data will also be collected after 12 and 24 weeks for outcomes, and data on the primary outcome, wound healing, will be collected biweekly. All data analysis will be performed using SPSS Statistics v21.0 (IBM). A two-tailed approach will be used, with *α* level set to 0.05 for testing. To ensure that outcome evaluators and data analysts are not influenced by group assignment, they will not interact with participants, except in the case of outcome evaluators during data collection. Descriptive statistics will be used to summarize demographic and other baseline characteristics. Tests of normality of data distribution were validated using Kolmogorov–Smirnov. After approaching normality for each variable, two-sample independent *t*-tests, x^2^-tests (or Fisher’s exact tests), or nonparametric tests, as appropriate, were used to compare normally distributed variables between the intervention and control groups. If necessary, the results will be adjusted based on potential confounding factors such as age, gender, and education level. Statistical analysis will be based on the intention-to-treat (ITT) method (34).

Generalized linear mixed effects models (GLMM) will be used to estimate the odds ratio (OR) and 95% confidence intervals (CIs) for assessing whether changes in outcome indicators are significantly different over time. Models include randomized groups with time as a fixed effect and time × group as an interaction effect to account for the correlation between repeated observations for each participant. Characteristics such as patient age, gender, wound type, and wound size will be adjusted for as covariates. In addition, to explore the effect of baseline characteristics on intervention effect sizes, we will conduct subgroup analyses by testing for interactions between subgroups and intervention effects. Predefined subgroup analyses will be conducted for baseline characteristics including age, gender, education, monthly income, wound type, and wound size. The main outcomes of the subgroup analyses are *p*-values for the group × time × characteristics interaction coefficients and estimates (95% CIs) of the differences between the intervention and control groups within each subgroup. Finally, sensitivity analyses will be performed by interpolating missing data using a random forest model to improve the reliability of our findings.

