#### Criteria for discontinuing or modifying allocated interventions

Every participant has the right to withdraw from the trial at any time. Participants will be terminated from the trial if, in the opinion of the investigator, it is necessary to do so for any reason, including ineligibility, adverse events, withdrawal of consent. Participants randomly assigned to the intervention group had the option of participating in traditional hospital wound treatment in the control group if they did not want to continue with the intervention. If a participant withdraws due to a related adverse event, the investigator will schedule a follow-up visit or phone call until the adverse event is resolved or stabilized. Adverse events unrelated to the intervention will be followed up until completion of the trial. Participants who stop the trial will have anonymized data collected until the exit time point. Any assessments not completed will be considered missing data. The reason for withdrawal will be recorded. Participants who withdraw after being randomized will not be replaced. Participants found to be ineligible after randomization will be withdrawn and no further data will be collected thereafter.

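### The only named sensitivity analysis, random-forest filling of missing data, assumes missing-at-random as the GLMM does, so it cannot test outcome-dependent drop-out; done as a single fill-in it would also distort the estimate or its standard error

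*Protocol article*

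**What the plan says.** The section on data collection and statistical analysis plans t-tests, chi-square or Fisher tests, or nonparametric tests between arms, and a GLMM with group, time and their interaction, all under intention-to-treat. It closes with the only sensitivity analysis in the document: "sensitivity analyses will be performed by interpolating missing data using a random forest model to improve the reliability of our findings". It does not say whether the filling is single or multiple, whether arm is a predictor, or how imputation uncertainty enters the standard error.

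The section on discontinuing or modifying allocated interventions says that a participant who leaves the trial contributes data only up to leaving, and adds: "Any assessments not completed will be considered missing data". The Sample section allows for substantial loss: "Assuming a drop-out rate of 20%, a total of 100 participants will be needed, with 50 participants in each group".

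**The concern.** A sensitivity analysis is useful when it changes an assumption the main result depends on. Here the assumption at risk is that patients who leave would have fared like similar patients who stay. The document gives reasons to doubt it:

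- Participants and treating staff know the allocation.
- Visit burden differs sharply by arm: clinic attendance every second day in the control arm, against weekly video and fortnightly home visits.
- Only the intervention arm is excused on-site service fees.
- Adverse events are among the reasons for ending participation.

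Reasons for leaving, and their link to the wound's course, could therefore differ by arm. None of this proves informative drop-out, but it makes it the scenario worth testing.

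There is a second, conditional worry. If each gap receives one forest prediction and the completed table is analysed as if observed, predictions count as full data. The check then returns a distorted effect or an interval that is too narrow, and would be read as confirming the findings.

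**Working it through.** **1. The plan's own figure.** Inputs from the Sample section: "μ1 = 38.64, μ2 = 32.54, *σ* take 8.21", 90% power, two-sided 5%. The difference is 38.64 − 32.54 = 6.10 (no unit is given; presumably days). Power by the noncentral t distribution is 0.8996 at 39 per arm and 0.9069 at 40, so 40 per arm is right. Then 40/(1 − 0.20) = 50 per arm, 100 in total. The figure reproduces.

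**2. What two missing-at-random analyses both miss.** Let a share p of one arm drop out, and let their true mean be worse by δ than observed data predict. Both a likelihood-based GLMM and a forest imputation then miss that arm's mean by p × δ. With p = 0.20 and assumed δ of 5 or 10, the estimated difference is off by 1.0 or 2.0, which is 16% or 33% of 6.10. δ is an assumption; observed data cannot supply it. Making the imputation multiple does not change this.

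**3. A single fill-in, by formula (50 per arm, 20% missing).**
- Honest standard error with 40 observed per arm: 8.21 × √(2/40) = 1.84.
- Reported standard error when 10 mean-type predictions per arm count as data: 8.21 × √0.8 × √(2/50) = 1.47. Ratio 1.47/1.84 = 0.80, so up to 20% too small if the fill-in respects arm.
- If arm is left out and predictors are baseline variables balanced by randomization, filled values carry no arm contrast. The expected effect is 0.8 × 6.10 = 4.88, and the estimator's true spread is about 0.8 × 1.84 = 1.47. The reported 1.47 is then right, but for a biased estimate.

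**4. A single fill-in, by simulation.** Settings: 50 per arm, SD 8.21, true effect −6.10 (intervention minus control), missing completely at random, 600 replicates per scenario, forest of 30 trees with minimum leaf 5 and four covariates, analysed by t-test. Each cell gives results for assumed covariate R² of 0.1, then 0.5. Type I error comes from runs with no true effect; its Monte Carlo error is about 0.9 points.

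| Missing | Method | Mean effect | Reported SE | Actual SD | Type I error |
|---|---|---|---|---|---|
| 20% | complete cases | −6.11, −6.14 | 1.82, 1.82 | 1.82, 1.87 | 5.0%, 5.0% |
| 20% | arm in forest | −5.61, −5.59 | 1.48, 1.51 | 1.76, 1.77 | 7.7%, 7.2% |
| 20% | arm left out | −4.89, −4.90 | 1.51, 1.54 | 1.47, 1.54 | 5.5%, 5.7% |
| 10% | arm in forest | −5.89, −5.94 | 1.57, 1.57 | 1.73, 1.64 | 6.7%, 5.3% |
| 10% | arm left out | −5.49, −5.58 | 1.58, 1.59 | 1.58, 1.55 | 5.5%, 5.0% |

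At 20% missing with arm in the forest, attenuation is 1 − 5.61/6.10 = 8%, and the standard error is 1 − 1.48/1.76 = 16% or 1 − 1.51/1.77 = 15% too small. With arm left out, attenuation is 1 − 4.89/6.10 = 20%, as the formula predicts. At 10% missing, attenuation is about 3% (arm in) or 9-10% (arm out), and with arm in, the standard error is 4-9% too small.

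A smaller simulation (250 replicates, 60 trees, baseline correlation 0.5, effect 6.10/8.21 = 0.743 SD) shows the same pattern. Arm in: effect 0.682, reported SE 0.184 against actual 0.235 (22% too small). Arm out: effect 0.608, SE 0.188 against 0.190. With 250 replicates the actual SD is itself known only to about 1/√(2 × 249) = 4.5%, so 15-20% is the fairer range.

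**The case against.** A reader might infer that the plan commits to a single fill-in that both shrinks the effect and understates the standard error. The text does not support that. Single is only the natural reading of the wording; a random forest inside multiple imputation is not excluded. The number of imputations, the predictors and the pooling are details that an article may leave to a fuller document, so their absence is not itself a fault. Nor do the two harms arrive together at full strength: leaving arm out costs mainly bias, with near-nominal type I error, while including it costs mainly precision that is not real.

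The simulation is also not this trial. It has one continuous outcome, an assumed covariate strength and benign missingness. The trial records wound scores every two weeks and images weekly, and a late leaver's earlier measurements could make predictions much better and both distortions smaller. The 20% is a planning allowance, not a forecast for each outcome.

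On informative drop-out, worsening recorded before exit is observed and usable, withdrawal reasons are recorded, non-attenders are contacted, intervention patients may move to clinic care without leaving the trial, and data collectors and statisticians are to be blinded. Forest imputation also makes a weaker assumption than t-tests on observed cases, so it is not an empty check against those.

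All of this stands, and it limits the second worry to a conditional one. It does not answer the first: nothing named departs from missing-at-random, and change after exit stays out of reach of any method that only predicts from observed data.

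**Conclusion.** The point holds in two parts. Unconditionally, the one named sensitivity analysis shares the GLMM's missing-at-random assumption, so agreement between them would not show robustness to outcome-dependent drop-out. Conditionally, a single fill-in analysed as observed data at 20% missing would attenuate the effect by about 8% with a standard error about 15-20% too small (arm in the forest), or by about 20% with a standard error about right for the biased estimate (arm left out). These sizes rest on missingness completely at random, assumed covariate R² of 0.1 to 0.5 and a single outcome measurement, and are smaller at 10% missing.

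It would be wrong to conclude that the main result is compromised. The primary estimate does not use the fill-in, and the sample size of 40 evaluable per arm, 100 in total, reproduces. This is a cheap improvement to a secondary analysis.

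**What to change.** Restate the sensitivity analysis as multiple imputation, with arm in the imputation model or imputation done within arm, at least 20 imputations, and results pooled by Rubin's rules. A random forest may remain the prediction engine inside chained equations, and the biweekly and weekly wound measurements should be among its predictors.

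Add a delta-adjusted or tipping-point analysis in which imputed outcomes of participants who left are made progressively worse, with the shift varied separately by arm, and report the shift at which the conclusion changes.

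The cost is a few sentences in the analysis plan, a few hours of programming and slightly wider intervals for the sensitivity analysis (a standard error near 1.84 rather than 1.47 on the design figures, somewhat lower if covariates predict well). Recruitment, visits and sample size do not change.

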### Data management and quality control

Data from medical records and questionnaires will be collected and stored in a secure electronic data capture system, named “the chronic disease management system.” Other raw data files will be securely stored online and securely transferred to the statistics team for analysis. Patient wound images will be transferred to an online server for 3D artificial intelligence algorithms to reconstruct the wound. Files will be linked to the database only through unique participant identifiers.

The data collection system will utilize a rigorously designed logical progression and conditional constraints to improve the accuracy and efficiency of questionnaire completion. Data collectors will undergo two rounds of standardized online training upon onboarding to ensure proficiency in the use of the data collection system and a uniform understanding of the collected item content. All data collectors will take an online exam and only those who pass the exam will be allowed to proceed to the formal data collection phase. The quality control team will scrutinize each entry in the dataset to prevent any incorrect or missing data.

#### Phase V: Long-term

In the last step, based on the results of the above research, a DE-HBWC implementation plan will be developed that can be continuously implemented in the long term to promote application. The long-term implementation plan is anchored in a multi-stakeholder, data-driven approach. Drawing from barriers identified in Phase III and adherence metrics from Phase IV, we will advocate for policy reforms to institutionalize home-based wound care. Continuous quality improvement will be enabled by a digital dashboard tracking healing rates and caregiver burden, with annual audits informing protocol refinements. Sustainability will be ensured through public-private partnerships for technology maintenance and community health worker training programs. During implementation, the plan can be dynamically adjusted as necessary to make it suitable for real-world implementation.

Firstly, we plan to include the DE-HBWC program in the hospital’s yearly goals and try to get it covered by Medicare. We’ll set up a special fund for things like telemonitoring equipment, nurse training, and patient support. Secondly, we’ll create a group of wound care experts from different hospital areas. They can consult and refer tough cases through our platform. We’ll also work with information technology to update the AI algorithms every year. Next, we’ll make a standard operating manual for DE-HBWC. We’ll provide toolkits with protocol templates, training courses, and data collection tools to make it easier to implement. We’ll break down components like training, technology, and policies into modules so that different hospitals can adapt them as needed. Then, we’ll train the first batch of certified wound specialist nurses and create a “DE-HBWC certified nurse” qualification with performance incentives. Lastly, we will set up a patient advisory board and hold feedback meetings every 6 months. We will focus on and address the top three improvement suggestions, such as simplifying the app operation process.

#### Scale: monitoring and evaluation

The implementation of interventions will be scientifically monitored and evaluated in the third to fifth stages of the research design and methods section. Furthermore, after completion of the 12-week DE-HBWC program intervention, we will perform a 12-week randomized controlled trial to evaluate the impact of an “incentive” implementation strategy within the DE-HBWC intervention group. This trial will assess both adherence rates (e.g., completion of remote assessments) and clinical outcomes (e.g., wound healing progression) to determine the strategy’s efficacy in optimizing engagement and therapeutic success. The “incentive” implementation strategy involves providing small financial reimbursements to participants in the intervention group to enhance adherence to telehealth consultations and data submission. This strategy is distinct from the clinical components of the core intervention (e.g., wound care protocols, AI monitoring) and serves solely to address behavioral barriers to participation. Control group participants receive identical clinical care without financial incentives.

#### Oversight and monitoring

The Trial Management Group, consisting of the Principal Investigator, the chief researcher, 1 nursing research staff member, 2 Wound specialist nurse, and 2 nursing master’s students, will meet on a monthly basis to oversee the study. The chief researcher will supervise the daily operation of the experiment and be responsible for the experiment.

#### Assessing adherence and strategies to improve adherence to the intervention

The compliance of patients in the intervention and control groups will be evaluated by measuring the rates of participation in online remote video visits, image acquisition, and offline wound treatment. If the patient does not participate as required, we will contact them via WeChat or phone. The intervention group will be exempt from on-site service fees. Two groups of patients who complete the prescribed number of interventions will have the opportunity to receive a reduction in wound treatment costs.

#### Criteria for discontinuing or modifying allocated interventions

Every participant has the right to withdraw from the trial at any time. Participants will be terminated from the trial if, in the opinion of the investigator, it is necessary to do so for any reason, including ineligibility, adverse events, withdrawal of consent. Participants randomly assigned to the intervention group had the option of participating in traditional hospital wound treatment in the control group if they did not want to continue with the intervention. If a participant withdraws due to a related adverse event, the investigator will schedule a follow-up visit or phone call until the adverse event is resolved or stabilized. Adverse events unrelated to the intervention will be followed up until completion of the trial. Participants who stop the trial will have anonymized data collected until the exit time point. Any assessments not completed will be considered missing data. The reason for withdrawal will be recorded. Participants who withdraw after being randomized will not be replaced. Participants found to be ineligible after randomization will be withdrawn and no further data will be collected thereafter.

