### Exclusion criteria

Patients who meet any of the following criteria will be excluded: (1) receiving palliative care or having malignant or fungal tumors, wounds with blind-end tracks such as sinus tracts, dry gangrene, exposed blood vessels, and other non-healing wounds; (2) suffering from mental illness or not cooperating with care; (3) suffering from autoimmune diseases or other serious comorbidities; and (4) hospitalized patients.

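### The withdrawal rules end outcome collection on some randomised patients without any withdrawal of consent, which conflicts with the stated intention-to-treat analysis

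*Protocol article*

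**What the plan says.** All but the analysis statements below come from the protocol article's section on criteria for discontinuing or modifying allocated interventions.

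- **Late-found ineligibility:** "Participants found to be ineligible after randomization will be withdrawn and no further data will be collected thereafter".
- **Investigator termination:** "Participants will be terminated from the trial if, in the opinion of the investigator, it is necessary to do so for any reason". Ineligibility, adverse events and withdrawn consent are named as examples.
- **Data after stopping:** "Participants who stop the trial will have anonymized data collected until the exit time point", and then "Any assessments not completed will be considered missing data".
- **Replacement:** "Participants who withdraw after being randomized will not be replaced".
- **Continued follow-up:** the section describes it for adverse events only, not for wound outcomes.

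The section on data collection and statistical analysis states: "Statistical analysis will be based on the intention-to-treat (ITT) method". It plans a generalised linear mixed model on the repeated measurements. It also says that "sensitivity analyses will be performed by interpolating missing data using a random forest model", and this is the only sensitivity analysis it names.

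**The concern.** An intention-to-treat comparison keeps the protection of randomisation only if outcomes are sought on everyone randomised. Here the protocol itself tells staff to stop collecting, in situations where the patient may be perfectly willing to be followed. This is a stated rule, not a detail left to an analysis plan. An analysis plan can define who is in the analysis set, but it cannot supply healing, BWAT or cost data that nobody gathered.

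The loss need not be neutral. Adverse events are a named ground for termination and may go with poor healing. The section on randomisation and blinding says that participants and intervention staff know the allocation. The arms also differ in planned in-person contact: home visits every two weeks against clinic attendance every other day. Problems that lead to termination may therefore come to light at different rates. If loss depends on the unseen outcome and differs between arms, the healing comparison is biased.

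**Working it through.** **1. The plan's own figure.** Inputs from the Sample section: means 38.64 and 32.54, SD 8.21, power 90%, type I error 5% (two-tailed, per the analysis section).

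- Difference: 38.64 − 32.54 = 6.10.
- Power of the two-sample t-test (noncentral t): 0.8996 with 39 per arm and 0.907 with 40 per arm, so 40 is the smallest number that reaches 90%.
- Drop-out: 40 / (1 − 0.20) = 50 per arm, 100 in total.

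The stated sample size reproduces and is not in dispute.

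**2. The rules side by side.**

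| Situation after randomisation | Outcome data under the protocol | What intention-to-treat needs |
|---|---|---|
| Found ineligible | None after withdrawal | Collected to T1/T2 |
| Terminated by the investigator | Up to exit, then missing | Collected to T1/T2 |
| Patient withdraws consent to data collection | Up to exit, then missing | Stopping is legitimate |

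The first two rows conflict with the analysis statement. The third does not.

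**3. Whether the planned analysis repairs the loss.** The mixed model and the random-forest fill both predict from what was observed. If patients with the same observed history differ in their later outcome according to whether they were withdrawn, neither method can see it.

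**4. Possible size.** The documents give no count or pattern of such withdrawals, so this step is an assumption throughout.

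Assumed: no true difference; normal healing times with SD 8.21; 45 per arm, midway between the 40 evaluable and 50 randomised, (40 + 50) / 2; *k* patients lost entirely from one arm; two-sample t-test at two-sided 0.05. The rate counted is a significant result favouring the arm with losses (nominally 2.5%). Each case has 40,000 simulated trials.

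| *k* lost from one arm | Random from the slower half: shift in mean; false-benefit rate | Exactly the slowest: shift in mean; false-benefit rate |
|---|---|---|
| 0 | 0; 2.5% | 0; 2.5% |
| 2 | about −0.3; about 3.5% | about −0.8; about 7% |
| 3 | about −0.5; about 4.3% | about −1.1; about 10% |
| 5 | about −0.8; about 6% | about −1.7; about 18% |

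Hand check of the slower-half shift: the mean of the upper half of a normal distribution lies 0.798 × 8.21 = 6.55 above the overall mean, so the shift is −*k* × 6.55 / (45 − *k*). For *k* = 2, 3 and 5 this gives −0.30, −0.47 and −0.82. The design difference is 6.10.

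Two reference cases:

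- Loss of the same numbers wholly at random leaves the two-sided error at about 5% (run with 50 per arm).
- Loss of the *k* slowest from both arms gives no average shift and a one-directional rate between about 3.4% and 4.4%.

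**The case against.** **The exclusion criteria as outcomes.** A reader might infer that patients who do badly will be declared ineligible and dropped, because the exclusion criteria include "and other non-healing wounds; (2) suffering from mental illness or not cooperating with care" as well as hospitalised patients. The documents do not support this as the plan's meaning. Table 2 places eligibility assessment at 0 weeks only, and late-found ineligibility reads most naturally as a baseline fact discovered late. Nothing says that a patient who is hospitalised or unco-operative after randomisation is withdrawn. The adherence section says that non-participants are contacted. The outcome-driven reading is possible only because the wording does not rule it out.

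**Blinding.** A reader might also infer that the person deciding on termination is unblinded. The protocol says so of participants and intervention staff, not of the investigator. Data collectors and statisticians are blinded. That does not help once collection has stopped.

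**The analysis set.** No one is expressly removed from it, data up to exit are kept, and BWAT is recorded every two weeks with weekly images. The mixed model uses those trajectories, so a patient who leaves late is not simply deleted. This softens the effect, but it does not cure loss that depends on unseen outcomes.

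**Switching.** Intervention patients may move to clinic treatment, but the text does not say that this ends their follow-up, so it is not part of the defect.

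**Size.** The rules are worded identically for both arms, and losing exactly the slowest healers from one arm is an extreme. Both points stand, which is why a range is given.

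**Conclusion.** The conflict is real: the protocol promises intention-to-treat while ordering that outcomes of some randomised patients not be collected, for reasons other than refusal of data collection. The resulting bias is a risk, not an established fact. Its direction and size depend on how many patients are lost, whether the loss tracks healing, and whether it differs by arm, and the documents settle none of these.

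Under the stated assumptions, two to five such losses from one arm take the false-benefit rate from 2.5% to somewhere between about 3.5% and 18%. The upper end requires the lost patients to be exactly the slowest healers, with none of their earlier data used. The claim that the worst outcomes will be removed from one arm goes beyond the text. The narrower claim, that the rule leaves avoidable and possibly informative gaps which the planned methods cannot correct, holds.

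**What to change.** Revise the section on discontinuing or modifying allocated interventions, and reconcile it with the analysis section, as follows:

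1. Treat leaving the allocated intervention, for whatever reason, as separate from leaving follow-up.
2. Continue to collect healing, BWAT and cost to T1 and T2 on every randomised patient, by visit, image or hospital record, unless the patient withdraws consent to data collection.
3. Analyse all randomised patients in the group to which they were allocated.
4. State that late-found ineligibility refers only to facts present before randomisation, and that it removes no one from follow-up or analysis.
5. Alongside the random-forest analysis, add a delta-adjusted sensitivity analysis in which patients with missing outcomes are assumed to heal progressively more slowly than the model predicts.

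The cost is a change of protocol and consent wording and some extra follow-up contacts or record checks. The sample size stays at 100. If all 50 per arm were evaluable, power on the plan's own inputs would be about 95.7%, against 90.7% with 40. The change should be made before or during recruitment, because outcomes not collected at the time may not be recoverable. Decisions on stopping treatment stay with the investigator, and no clinical rule is proposed here.
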